### 3.5. Variables (Identification, Definition, and Measurement Scales)

#### 3.5.1. Definition of Variables

Dependent-variable of interest: Incidence of hypertension.Independent-variables of interest: Periodontal-related parameters and oral-related microbial profiles.Oral health covariates: Oral health related quality of life; diet changes; perception of need for dental treatment; xerostomia; use and functionality of removable dental prostheses; oral hygiene (presence of biofilm and dental calculus); number of natural teeth present; dental caries; root debris and gingival bleeding.

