#### 3.9.5. Gingival Bleeding

Gingival bleeding will be measured with the *Bleeding On Marginal Probing Index (BOMP)* defined by Van der Weijden et al. (71). BOMP will be recorded after inserting a PCP UNC15 periodontal probe (WHO-Hu Friedy^®^) along the marginal gingiva (~2 mm) and held at an angle of ~60° to the longitudinal axis of the tooth according to the Angulated bleeding index (AngBI); bleeding will be scored within 30 s after probing (71).

The clinical parameters will be assessed at six sites per tooth: distobuccal, buccal, mesiobuccal, distolingual, lingual and mesiolingual. Gingival units that bleed on probing will be recorded as follows: giving non-bleeding sites a score = 0, bleeding at one point a score = 1, excessive bleeding a score = 2. This index has been used in several studies and provides specific information for every gingival unit as reported in the update by the group of Van der Weijden (72). A participant will be considered to have gingival bleeding when at least one gingival margin is rated one or higher.

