## 4. Data Collection

Participants in the umbrella cohort who meet the inclusion criteria will be invited to participate in this study. The purpose of the study will be explained to them and they will be asked to sign an additional informed consent document. An appointment will be scheduled to carry out the oral health interview, dental clinical examination and sampling for the saliva and subgingival microbiota analysis at the facilities of the Graduate Studies and Research Division of SD-UNAM. The clinical examination will be performed with the person sitting in the dental chair under artificial light. It will be explained to them that strict infection control measures will be used and that all instruments will be sterile and for their exclusive use. In the event that something unusual is observed during the dental examination, the participant will be informed that it is necessary for a dentist to examine it in more detail and will be referred to the SD-UNAM clinics. To record the data an encoder will fill-in the information in the corresponding format.

The full study will be organized in five exploration stages mentioned below: 1) reception of participants, 2) collection of biological samples, 3) interviews and anthropometric measurements, 4) oral examination and 5) sample processing (see Figure 2).

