### 5.1. Methods Collection

Sampling of saliva and subgingival plaque will be performed at baseline and at the end of follow-up in the participants selected for the oral microbiome analysis. All participants will be asked to stop taking antibiotics 3 months before and to stop mouthwashes—1 week before the clinical examination. History of occasional antibiotic consumption (outside sampling dates) will be recorded and analyzed. They will also be asked to stop tooth brushing 24 h before the clinical exam. They will be asked to refrain from eating, drinking anything other than water and chewing gum for 12 h prior to taking samples (76).

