#### 5.1.2. Subgingival Dental Biofilm Sampling

Following saliva collection, subgingival plaque samples will be collected for microbial evaluation analysis. After drying and isolating with cotton rolls, visible supragingival plaque will be removed and discarded. Then subgingival plaque sampling will be performed from the mesiobuccal zone of first molars (or if missing, second molars or premolars) (80, 81) of each quadrant (82, 83) with an individual sterile Gracey curette (Mini-Five #SAS11/122). The Gracey Curette will be inserted deep into the gingival sulcus of the periodontal pockets without tooth contact, angled to get in close contact to the tooth root surface to carefully scrape off the biofilm (84, 85). Then each subgingival sample will be deposited into an individual sterile tube with a buffer solution.

All samples from an individual participant will be immediately placed and dispersed into the same tube containing 150 μl of TE buffer (10 mM Tris-HCl, 0.1 mM EDTA, pH 7.6). The teeth for which the sample will be taken will be recorded in the data collection format. The tube will be placed in an IsoTherm system (IsoSafe Transport Box, 0°C and IsoRack for 1.5 mL tubes) Eppendorf^*TM*^ and delivered to the laboratory for processing within 4 h of obtaining the sample. The relative microbial abundance analysis will further proceed following the same procedure described for saliva samples in the previous subsection.

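### Biofilm and gingival bleeding are scored after a 24-hour brushing stop and after curette sampling; the hygiene adjustment variable and the one-margin bleeding rule should be settled accordingly

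*Protocol article*

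**What the plan says.** **Preparation.** Section 5.1 opens with who is sampled and when: "Sampling of saliva and subgingival plaque will be performed at baseline and at the end of follow-up in the participants selected for the oral microbiome". It then gives the preparation rules: "All participants will be asked to stop taking antibiotics 3 months before and to stop mouthwashes—1 week before the clinical examination". The brushing rule follows: "They will also be asked to stop tooth brushing 24 h before the clinical exam".

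**Order of the visit.** Section 4 lists the stages as "1) reception of participants, 2) collection of biological samples, 3) interviews and anthropometric measurements, 4) oral examination and 5) sample processing".

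**Sampling.** Under Section 5.1.2, "visible supragingival plaque will be removed and discarded". A curette is then inserted into the sulcus at the mesiobuccal site of one molar (or a substitute tooth) per quadrant, and the teeth used are recorded.

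**Scoring.** Section 3.9.1 scores biofilm and calculus on the buccal and lingual surfaces of all natural teeth. Section 3.9.5 scores bleeding at six sites per tooth and then reduces it to yes or no: "A participant will be considered to have gingival bleeding when at least one gingival margin is rated one or higher".

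**Use.** Section 3.5.1 lists gingival bleeding among the oral health covariates, together with "oral hygiene (presence of biofilm and dental calculus"). Hypothesis 1 in Section 2.3 instead controls for oral hygiene habits, which the Section 3.4 questionnaire collects. Section 9.1.2 evaluates the incidence of each oral variable and uses trajectories of oral conditions as risk factors for hypertension.

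**The concern.** Two covariates are measured after the study has acted on them.

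- **Biofilm.** It is scored after a day without brushing, so it no longer describes usual hygiene. In sampled people, plaque has also been removed around the sampled sites.
- **Bleeding.** It is scored after a curette has been in four sulci, and one positive margin decides the participant's class.

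A covariate with this kind of error adjusts poorly. If the error differed by periodontitis status, adjustment could leave confounding behind or remove part of the periodontitis effect. Oral hygiene is one of the few confounders that hypothesis 1 names, and the protocol gives two candidates for it: habits in Section 2.3, biofilm and calculus in Section 3.5.1.

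**Working it through.** **Inputs.** Cohort 1,212, planned 10% with and 90% without periodontitis (Section 3.3.1). Microbiome subsample 100 with and 100 without (Section 3.3.2). Periodontitis prevalence of 30–50% in developed countries (Introduction), used as a range. Six sites per tooth (Section 3.9.5), two surfaces per tooth (Section 3.9.1), one sampled site per quadrant (Section 5.1.2). Assumption: 28 teeth present, so 28 × 6 = 168 margins and 28 × 2 = 56 surfaces.

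**1. The plan's own figure.** 200 people × 2 sample types = 400 samples per evaluation time, 200 per periodontal group. This agrees with Section 3.3.2.

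**2. Reach of the curette.** 4/168 = 2.4% of margins. Plaque is removed from at most about 4/56 = 7% of scored surfaces. This is small for a percentage score, but enough to decide a one-margin rule.

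**3. Contrast of the one-margin rule.** With site rate s and independent sites (an assumption), the share classed as bleeding is 1 − (1 − s)^168.

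- s = 1%: 1 − 0.99^168 = 0.815
- s = 2%: 1 − 0.98^168 = 0.966

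This holds before any curette contact. Bleeding that clusters within mouths would lower these shares at the same average site rate.

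**4. Share sampled in each group, if sampling is confined to the 200.** With prevalence p, the shares are 100/(1,212p) and 100/(1,212(1 − p)).

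| p | With periodontitis | Without |
|---|---|---|
| 10% | 100/121 = 82.5% | 100/1,091 = 9.2% |
| 20% | 41.3% | 10.3% |
| 30% | 27.5% | 11.8% |
| 40% | 20.6% | 13.8% |
| 50% | 16.5% | 16.5% |

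The same shares apply to the brushing stop if that too is confined to the 200.

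**5. What this could do to the yes/no bleeding variable.** Let true bleeding be b in both groups, and let q be the chance that sampling alone turns a non-bleeder positive. Both are assumptions; the protocol gives neither. The observed share is b + (1 − b) × f × q, with f the share sampled.

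- p = 10%, b = 0.5, q = 0.5: 0.5 + 0.5 × 0.825 × 0.5 = 70.6%, against 0.5 + 0.5 × 0.092 × 0.5 = 52.3%. Gap 18 points.
- p = 10%, q = 0.5: gap 7 points at b = 0.8 and 2 points at b = 0.95.
- p = 30%, b = 0.5, q = 0.5: gap 4 points.
- p = 50%: gap 0.

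**6. Biofilm.** No figure in the protocol gives the effect of 24 hours without brushing on the score. The brushing stop raises plaque and the wiping lowers it on a few surfaces. Only the direction of each step can be stated, not the net size.

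**The case against.** A reader might infer that the two covariates are distorted unequally between the periodontitis groups, and that the main association is therefore biased. The document does not support either step.

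- **Unequal distortion.** The preparation rules are addressed to all participants, and Section 4 schedules interview, examination and sampling in one appointment without naming a subset. Read that way, the brushing stop is equal in both groups. Restricting sampling to 100 and 100 by periodontitis status also needs the diagnosis beforehand, yet in the listed order probing is at stage 4 and sampling at stage 2. The 82.5% versus 9.2% contrast is one scenario.
- **Main estimate.** Hypothesis 1 names habits, which come from a questionnaire that the preparation does not touch. Bleeding is not in that adjustment set.
- **Size.** Few sites are touched. If bleeding on at least one margin is already near-universal, the curette can reclassify few people.
- **Standardisation.** A uniform time since last brushing is a defensible way to standardise, and calculus is not plausibly changed in a day.
- **Order.** The flow chart in Figure 2 is not available here, so the order rests on the numbered stages in the text.

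All of this stands as a limit on size. It does not remove three facts: the order as written puts scoring after preparation and sampling, the protocol labels two different things as oral hygiene, and the bleeding rule can be decided by a single sampled site.

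**Conclusion.** The point holds as a measurement and definition problem that is cheap to correct. It is not a demonstrated bias in the periodontitis–hypertension estimate.

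The biofilm score reflects a day without brushing. The yes/no bleeding variable can be turned positive by sampling and has little contrast even without it: 82% to 97% positive at site rates of 1% to 2%, assuming 168 independent margins. Inequality between groups is conditional on confinement to the 200 and on periodontitis well below 50%.

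The effect on the main estimate is limited if the model uses the questionnaire habits of Section 2.3. Section 3.5.1 leaves room for the biofilm score to be used instead, so the two sections must be reconciled.

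**What to change.** 1. **Hygiene adjustment.** State that hypothesis 1 uses the oral hygiene habit items (Sections 2.3 and 3.4), with calculus if wanted, and not the biofilm score taken after the brushing stop. Align Section 3.5.1 with this. State in Section 5.1 who stops brushing and before which examinations.
2. **Bleeding and biofilm scores.** Analyse bleeding as the percentage of margins scoring 1 or more, in place of the one-margin rule. Leave the sampled sites out of the bleeding and biofilm percentages. Add a sensitivity analysis that drops the first molars in everyone, so that sampled and unsampled people are scored on the same teeth.

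**Cost.** Changes to wording and variable derivation only: bleeding is recorded per gingival unit and the sampled teeth are recorded, so no new visits or data are needed. The downsides are that habit items are self-reported and that two indices lose a few sites.

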#### 5.1.1. Saliva Sampling

Sampling of saliva will be collected in the morning (between 7:30 and 10:30 a.m.). Fully non-stimulated saliva samples will be collected spitting saliva for at least 1 min, as previously reported (77) into a sterile and pre-labeled Falcon 15-mL tube. This process will be repeated until a total volume of 2 mL is collected. Saliva samples will be divided into two 1 mL aliquots, centrifuged for 10 min at 13,200 RPM, the supernatant will be discharged, and solutions will be re-suspended in 150 μl of TE buffer prior to DNA purification.

For the detection of all the bacterial species present in saliva and subgingival dental plaque samples, DNA samples will be previously isolated and purified for the sequencing of the conserved and hypervariable regions of the RNA of the 16S ribosomal gene (16S rRNA Seq). The gene-specific sequences used in this protocol target the 16S V3 and V4 region. They are selected from Klindworth et al. (78). This experimental strategy is an alternative that circumvents the limitations of microarray-based approaches, which by necessity have a pre-established panel of microbial species. 16S rRNA is a gene universally present in prokaryotic organisms; therefore, by using the so-called “universal primers,” it will be possible to detect all the species present in a sample. To this end we will follow the experimental design of the *Human Oral Microbiome Project*, adapting it for NGS sequencing of the 16S rRNA region (79).

#### 5.1.2. Subgingival Dental Biofilm Sampling

Following saliva collection, subgingival plaque samples will be collected for microbial evaluation analysis. After drying and isolating with cotton rolls, visible supragingival plaque will be removed and discarded. Then subgingival plaque sampling will be performed from the mesiobuccal zone of first molars (or if missing, second molars or premolars) (80, 81) of each quadrant (82, 83) with an individual sterile Gracey curette (Mini-Five #SAS11/122). The Gracey Curette will be inserted deep into the gingival sulcus of the periodontal pockets without tooth contact, angled to get in close contact to the tooth root surface to carefully scrape off the biofilm (84, 85). Then each subgingival sample will be deposited into an individual sterile tube with a buffer solution.

All samples from an individual participant will be immediately placed and dispersed into the same tube containing 150 μl of TE buffer (10 mM Tris-HCl, 0.1 mM EDTA, pH 7.6). The teeth for which the sample will be taken will be recorded in the data collection format. The tube will be placed in an IsoTherm system (IsoSafe Transport Box, 0°C and IsoRack for 1.5 mL tubes) Eppendorf^*TM*^ and delivered to the laboratory for processing within 4 h of obtaining the sample. The relative microbial abundance analysis will further proceed following the same procedure described for saliva samples in the previous subsection.

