#### 3.3.2. Sample Size for the Microbiological Studies

The sample size of the oral and subgingival microbiome study is projected to be 200 people sub-sampled in a randomized adjusted cohort design (100 subjects with periodontitis and 100 without periodontitis). This is so since the lower bound for the number of samples to probabilistically infer co-existence networks (in this case of microbial species) by the method we use (based on the calculation of the mutual information function) is ~100 per evaluated group (37). A total of 400 microbial samples per evaluation time (baseline and 60 follow-up months) will be placed 200 for periodontal health subjects and 200 for periodontitis subjects, with a subdivision of 100 for saliva and 100 subgingival samples each. Since the sequencing analysis for microbiota is relatively expensive it was decided to use just this number for experimental design. Sampling for microbiome analysis will be done in participants who have developed hypertension (with periodontitis and without periodontitis) and in those who have remained at normal blood pressure levels (with periodontitis and without periodontitis).

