#### 3.6.2. Periodontitis

The periodontal evaluation will be done every year in terms of probing pocket depth (PPD) and clinical attachment loss (CAL). Examining 6-site-per-tooth in all natural teeth—except third molars–, measuring the distance from the cemento enamel junction (CEJ) to pocket depth and the distance from the gingival margin to the CEJ will be performed. Participants will be divided into two groups: (1) participants without periodontitis and (2) those with a diagnosis of periodontitis (mild, moderate and severe) based on *Centers for Disease Control and Prevention and American Academy of Periodontology* (CDC/AAP) definition (47), suggested for epidemiological studies by Holtfreter et al. (48). According to a recent agreement among experts from Europe and USA (48) and recent epidemiologic trends, the 2012 CDC/AAP criteria become a consensus approach for epidemiological studies worldwide (49). Furthermore, the 2017 World Workshop on the Classification of Periodontal and Peri-Implant Diseases and Conditions (50), in Appendix B, recommended that *After a long-standing debate on how to provide data to inform surveillance of periodontal disease, a recent multinational effort has suggested standard reporting of periodontal epidemiology surveys. Such efforts are important to provide comparable data across populations*.

Several international research efforts have actually made use of this definition for periodontitis cases. For instance, a recent study (51) that compared CDC/AAP Case Definition and the EFP/AAP Classification concluded that use of the EFP/AAP classification (as a possible new globally accepted classification) to assess periodontitis prevalence, severity and risk factors when conducting epidemiological surveys may not be totally reliable for use in population surveys. Hence the use of CDC/AAP in these studies is deemed more appropriate. Also, a recent systematic review and meta-analysis of the association of periodontitis with hypertension determined the CDC/AAP as a confident case definition of periodontitis (3).

The implementation of this classification improved reporting quality and permitted meaningful comparisons of the prevalence of periodontal diseases across populations in epidemiological studies (48). Indeed, many recent epidemiological studies with diverse populations in different parts of the world have used this classification (52–57), as well as (58–61) and (61–63).

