For the sake of the present research and based on the international consensus just discussed, periodontitis cases will be classified as follows:

No periodontitis, there is no evidence of mild, moderate, or severe periodontitis.Mild periodontitis, is the presence of at least 2 interproximal sites with *CAL* ≥ 3 mm and at least 2 interproximal sites with *PPD* ≥ 4 mm (not on the same tooth) or 1 site with *PPD* ≥ 5 mm.Moderate periodontitis, defined as at least 2 interproximal sites with *CAL* ≥ 4 mm (not on the same tooth) or at least 2 interproximal sites with *PPD* ≥ 5 mm (not on the same tooth).Severe periodontitis, defined as having at least 2 interproximal sites with *CAL* ≥ 6 mm (not on the same tooth) and at least 1 interproximal site with *PPD* ≥ 5 mm.

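### Subgingival plaque comes from four position-fixed, pooled sites while periodontitis is labelled by whole-mouth criteria, so localised cases may contribute profiles with no diseased site and pull the health-versus-periodontitis contrast toward no difference

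*Protocol article*

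**What the plan says.** Section 5.1.2 fixes the sampled sites by position: "subgingival plaque sampling will be performed from the mesiobuccal zone of first molars (or if missing, second molars or premolars"), one per quadrant. The nearest it comes to site condition is "The Gracey Curette will be inserted deep into the gingival sulcus of the periodontal pockets without tooth contact". That sentence describes how the instrument is inserted. It sets no threshold of probing pocket depth (PPD) or clinical attachment loss (CAL) for choosing a site.

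On handling, the section says two things: "Then each subgingival sample will be deposited into an individual sterile tube with a buffer solution" and, directly after, "All samples from an individual participant will be immediately placed and dispersed into the same tube". It adds: "The teeth for which the sample will be taken will be recorded in the data collection format".

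The group label comes from a different source. Section 3.6.2 bases it on a full examination, "Examining 6-site-per-tooth in all natural teeth" apart from third molars. A moderate case needs two interproximal sites on different teeth, with CAL of at least 4 mm or PPD of at least 5 mm. The lowest category begins "Mild periodontitis, is the presence of at least 2 interproximal sites with" CAL of at least 3 mm, joined with two sites at PPD of at least 4 mm, or one at 5 mm or more. Section 9.1.2 merges mild, moderate and severe cases into one group and leaves severity to later, a posteriori use. The microbiome sub-sample in section 3.3.2 is "100 subjects with periodontitis and 100 without periodontitis".

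**The concern.** The exposure is a property of the whole mouth, but the measurement is a property of four sites chosen without regard to disease. A person can be a case because of sites that are never sampled. That person's profile then sits in the periodontitis group although all the plaque came from unaffected sites. Pooling adds to this: a case with one affected sampled site still contributes a tube in which three of the four sites are unaffected.

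The comparison at risk is a central one. Section 2.1 names the association of subgingival profiles with hypertension and periodontitis as the primary endpoint, and the second hypothesis in section 2.3 is the with-versus-without contrast in subgingival relative abundance. A weak or null result could not be told apart from an effect of where the plaque was taken.

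**Working it through.** **The plan's own figure.** Section 3.3.2 gives 400 samples per evaluation time. 200 people × (1 saliva + 1 subgingival) = 400, which reproduces. It also means one subgingival sample per person. Four separately analysed tubes would give 200 × (1 + 4) = 1,000, so the stated count fits pooling and not individual tubes.

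**Inputs.**
- Sampled sites: 4 (one per quadrant, section 5.1.2).
- Interproximal sites: 28 teeth × 4 = 112 (third molars excluded, section 3.6.2; four of the six sites listed in section 3.9.5 are mesial or distal).
- Number of diseased sites per case, k: not given. Assumed range 2 to 34.
- How much more often the sampled sites are diseased than other sites, w: not given. Assumed 1, 3 and 10.

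**Chance that no sampled site is diseased, random spread (w = 1).** P = C(112 − k, 4) / C(112, 4). For k = 2 this equals (108 × 107) / (112 × 111) = 0.930. Requiring the two sites to be on different teeth also gives 0.930. With 20 teeth (80 sites) it is 0.90.

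**Sampled sites more often diseased.** Diseased sites are drawn without replacement, with weight w on the four sampled sites. For k = 2 and w = 3 the total weight is 108 + 12 = 120, and P = (108/120) × (107/119) = 0.81. For w = 10 the total is 148, and P = (108/148) × (107/147) = 0.53. Larger k was simulated with 40,000 draws.

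| Diseased sites k | w = 1 | w = 3 | w = 10 |
|---|---|---|---|
| 2 | 93% | 81% | 53% |
| 4 | 86% | 65% | 28% |
| 10 | 68% | 34% | 4% |
| 20 | 45% | 10% | 0.1% |
| 34 (30% of sites) | 23% | 1% | 0% |

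**What dilution would do (illustration only).** The plan gives no effect size or power for this contrast. With 100 per group and two-sided 0.05, the difference detectable with 80% power is (1.96 + 0.84) × √(2/100) = 0.40 SD. Suppose a share f of case profiles contains no diseased site and looks like health. The mean difference becomes 0.40 × (1 − f).

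| f | Power |
|---|---|
| 0 | 80% |
| 10% | 71% |
| 25% | 56% |
| 50% | 29% |

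At f = 50% the sample size needed is 1/0.5² = 4 times as large.

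**The case against.** Sampling fixed index sites is a deliberate, referenced choice. It keeps profiles comparable between groups and between baseline and 60 months. That stands, and it is why the sites should not be changed.

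The plan is also not confined to the person-level label. Section 3.5.1 lists periodontal parameters as independent variables, section 9.2.4 relates the subgingival microbiome to clinical variables, and section 9.1.2 takes up severity later. Nothing rules out an analysis by sampled site, and an analysis plan that is not shown may contain one. This stands in part. However, whole-mouth severity is still not the state of the sampled sites, and the article itself fixes the sites, the pooling and the grouping that do not match.

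A reader might infer that most periodontitis profiles will come from healthy sites. The documents do not support this. They give neither the extent of disease nor how often first-molar sites are involved, and the table runs from 93% to nearly zero depending on both. Two diseased sites is close to the minimum for a case, not a typical one. Eligibility of healthy adults aged 20 to 50 makes limited disease plausible, but severe cases remain eligible and section 5 expects some.

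A reader might also extend the point to the hypertension contrast. That is not shown: hypothesis 3 compares people who do and do not develop hypertension, all sampled in the same way, and it also uses saliva, which is not tied to these four sites.

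**Conclusion.** The mismatch between sampled sites and case definition is real. Its direction is toward no difference in the subgingival health-versus-periodontitis contrast (hypothesis 2 and the periodontitis part of the primary endpoint). Its size cannot be fixed from the documents. For a case with 2 to 10 diseased sites, the chance of a profile with no diseased site is 68% to 93% under random spread and 34% to 81% at threefold weighting. In generalised disease it is small.

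These figures rest on 28 teeth, on the assumed k and w, and, for the power illustration, on unaffected sites in cases resembling sites in health. This is a weakness in sensitivity and interpretation that the study's own data can address at little cost. It does not make the sampling scheme wrong. Apart from the two tube statements, which conflict, it is not an internal contradiction.

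**What to change.** Keep the sampling sites, the randomised 100 + 100 sub-sample, the two-group contrast and the person-level networks. Add the following:

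1. From the six-site examination and the recorded sampled teeth, derive PPD and CAL at each sampled site.
2. Report the share of periodontitis cases with at least one affected sampled site. Define affected by PPD or CAL, because a moderate case can qualify on CAL alone and a PPD-only rule would misclassify it.
3. Prespecify one supportive abundance analysis. Its exposure is either sampled-site status (cases with an affected sampled site, cases with none, no periodontitis) or mean sampled-site PPD and CAL.
4. Reconcile the individual-tube and same-tube sentences in section 5.1.2 with each other and with the count of 400 samples.

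The cost is some wording, a derived variable and one extra analysis. Its subgroups are smaller than 100 whenever both case subgroups are non-empty, so it should not be used for network inference, where section 3.3.2 sets about 100 per group as the lower bound.

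Two further steps may look attractive but should not be taken. Favouring moderate or severe cases when drawing the 100 conflicts with the randomised sub-sampling. At the planning figure of 10% exposed there would be only about 0.10 × 1,212 = 121 cases for 100 places. Replacing the two groups with three would change the question asked by hypothesis 2.
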